### Participants and recruitment

Together with the *Bavarian Association of Family Physicians and General Practitioners,* the *Institute of General Practice at the University Medical Center Erlangen* (UHE) will recruit a total of 150 general practitioners (GP) from practices in Northern Bavaria. Two-thirds of the practices are randomized to the IG and one third to the CG. If a GP practice expresses interest after being invited to participate in the study, it receives information concerning the study, regulations for enrolling in the intervention program, and participation documents for the GP practice and the patients. After written consent to study participation and enrolment in the intervention program, the practice is formally included in the GAP trial. The UHE passes on registration data to the *Bavarian State Association of company health insurance fund*, which is responsible for the cooperation with the participating company health insurance funds. Over five quarters (July 2018 to September 2019), the GP practices are to recruit a total of 1000 patients for the IG and 500 for the CG. With an average share of at least 20% BKK insured persons, 900 patients per practice license in Bavaria and a back pain prevalence of almost 30%, the resulting recruitment potential is 50 to 60 patients per physician. The fact that physicians receive reimbursement for recruitment and patients receive a book voucher will facilitate sufficient recruitment.

#### Eligibility criteria for patients

Eligible are persons aged 18 years or older, insured by a company health insurance fund, presenting with back pain symptoms in a participating GP practice and providing written informed consent. Patients with insufficient German language skills to fill in the study questionnaires are excluded from the study.

#### Termination criteria

No termination criteria are defined for the overall study. The withdrawal of written consent is the termination criteria for the individual patient respectively physician. In the event of a withdrawal, deletion from the assignment list is ensured and the related questionnaires are immediately destroyed and erased from evaluation. Physicians and patients are informed that already processed data will still be used anonymously.

### Interventions and procedures

#### Description of the portal

Evidence-based information on treatment options for back pain is comprehensibly presented and made available as a login-required, password-protected online portal for participating physicians and patients. The portal focuses on frequently occurring issues in general practice related to back pain. It contains descriptive material, links to further information and suggestions for well-informed shared decision-making, self-responsible training and preventive lifestyle changes.

During consultation, the physician can show images, animations, infographics and videos from the portal to the patient, discuss the material, and provide the patient with a concise selection of information as a printout. To ease selection, the portal will contain four pre-structured information packages for common back pain problems:Acute non-specific lower back pain.Sub-acute non-specific lower back pain.Chronic non-specific lower back pain.Brief information on certain diseases causing specific lower back pain.

The information packages are designed to be highly accessible for physicians and patients and contain clearly navigable information on epidemiology, causes, symptoms, harms and benefits of treatment options and on the reliability of the given information. The evidence of recommended and not-recommended treatment options (such as physiotherapy, pain medication or bed rest) for the most common conditions are outlined including risks and side effects. Each package is designed to motivate navigation and quick understanding, and includes references to further information for physicians and patients. In addition, the patient receives multimedia instructions for self-management strategies and training. Furthermore, the portal provides two customized reference books for physicians and patients in order to enable the search for information by keywords.

For the physician, the portal includes user instructions and a brief guide on how to structure the consultation. The guide recommends the following established consultation pattern: (1) patient’s concerns and expectations, (2) physical examination, (3) working hypothesis or diagnosis, (4) therapy proposal and shared decision-making. For the patient, the portal includes explanations and guiding questions to prepare for a well-informed physician patient communication.

#### Procedures for physicians

Physicians in IC and CG fill out the primary outcome questionnaires at the following time points: before intervention (before accessing the portal (t0), directly after recruiting the last patient (t1), and 3 months after recruiting the last patient (t2). Data from the CG is gathered concurrently. Physicians in the IG are interviewed online, physicians in the CG via an online survey or, where appropriate, paper-pencil questionnaires (hybrid survey). Structural features of practices are collected once in an initial questionnaire in both IG and CG. After the intervention (t1) in the IG, usage, usability and accordance of information and information needs are surveyed. To test for enduring use, the usage of the platform is again measured at t2. Physicians in the CG continue to perform their usual consultation routines. The participating physicians of the IG and CG are given an incentive for study participation by the UHE at the end of the survey period. The incentive is calculated according to the number of recruited patients per physician (34 € per participating patient in IG and CG). Additionally, the physicians in the IG receive 40 € once per patient for the first consultation using the portal. The study protocol does not determine any limitations or specifications for further consultations or the care of the patients. Physicians of the IG are asked to use the portal during the consultation according to the instructions and the consultation guidance. To ensure appropriate usage of the portal, the UHE sets up a telephone hotline for the physicians in case of difficulties or questions. During the initial phase, the institute contacts each IG physician at least once proactively, and offers support. This proactive contact is made step by step. First, the physicians are contacted by email and asked whether support is needed. If there is need for support, telephone contact is offered and, if necessary, a personal visit is made. As an adherence indicator the frequency of portal usage per physician is measured via web analytics. 25 IG physicians are randomly selected and interviewed by the Institute of Medical Psychology and Medical Sociology (MPS) after inclusion of the last patient in semi-structured telephone interviews on portal acceptance, quality and practicability (implementation, supportive factors and barriers) and the perception of their own communication behaviour as well as the subjective evaluation of the consultation guidance.

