## Methods

The GAP trial uses a prospective multi-centre, cluster-randomized parallel group design in order to evaluate whether the use of the GAP portal on back pain is superior to routine care. The GAP project consists of three phases. (1) Within the pilot phase, the portal will be tested for usability by physicians and patients and adapted according to the pilot findings (Additional file 1: Development and piloting of the GAP portal). (2) The main trial (second phase) evaluates the effects on pre-defined outcomes in general practitioners and patients with back pain (Table 1). (3) Within the third phase, the potential benefit of web-based information for health problems other than back pain will be analysed (Additional file 2: Expanding of the GAP portal).

**Table 1 Tab1:** PICO question of the GAP trial

Research Question	What are the effects of using the back pain internet portal compared to standard care in patients with back pain?
Population	150 general practitioners and 1500 back pain patients in Northern Bavaria
Intervention	Using the portal during (physician) and after (patient) the consultation.
Comparison	Routine consultation (no use of the portal)
Outcomes	1. Physicians‘and patients’ informedness 2. Physician-patient-communication 3. Patients‘health literacy and self-efficacy expectation 4. Days of sick leave 5. Back pain related health costs

*Hypothesis on primary outcomes:* (1) After the consultation, the informedness and the quality of the physician-patient communication are rated significantly higher by general practitioners and patients who use the portal (intervention group, IG) than by those who do not (control group, CG, consultation as usual).

*Hypotheses on secondary outcomes:* (2) 3 weeks after the consultation, the patients’ informedness, health literacy and self-efficacy are significantly higher among those who use the portal than among those who do not. (3) 3 months after consultation, the number of days of sick leave as well as the utilization of health system resources is significantly lower among patients who use the portal than among those who do not.

*Design:* Prospective cluster RCT with pre-, post- and one follow-up-measurement and process evaluation.

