### Outcomes

*Primary outcomes,* which are assessed by questionnaires (survey data), are the quality of the patient-physician communication and patient informedness (Table 2). It is analysed whether values in the IG differ significantly from the CG.

**Table 2 Tab2:** Primary outcomes, instruments and measurement points

	t_0-physician_	t_0-patient_	t_1-patient_	t_2-patient_	t_1-physician_	t_2-physician_
Quality of the patient-physician communication (patient)						
Shared Decision-Making Questionnaire (SDM-Q-9) [38]			X			
Questionnaire on the communication behaviour of physicians (KOVA) [39]			X			
Scale “Satisfaction” of the P.A.INT-questionnaire [40–43]			X			
Quality of the patient-physician communication (physician)						
Scale “Effective and open communication” of the KOVA [39]^a,b^	X				X	X
Scales “Empathy”, “Openness and coherence”, “Positive regard and appreciation”, “Contact barriers” and “Satisfaction” of the P.A.INT-questionnaire [40–43]^a^	X				X	X
One Item of the Man-Son-Hing scale. [44]^a^	X				X	X
Shared Decision-Making Questionnaire (SDM-Q-Doc) [45, 46]^a^	X				X	X
Informedness (patient)						
Self-reported knowledge questionnaire^c^		X		X		
Self-reported knowledge global question^c^			X			
Perceived informedness questionnaire^c^				X		
Perceived informedness global question^c^			X			

^a^Instruments will be adapted so that physicians assess their communication behaviour across consultations

^b^Instrument will be adapted for assessing the communication from physician’s perspective

^c^These instruments will be developed for the project. The questionnaires will be checked for understandability and acceptance in a cognitive pretest using one-to-one interviews with eight patients having experienced back pain [47]

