### Data management

A seven-digit patient research ID (three-digit number for the practice, two-digit number for the attended physician and a consecutive two-digit number per patient attending the physician) is allocated to each participating patient. A database with these research IDs and the associated names and contact details of the patients (participation list) is created. Due to the research IDs the questionnaires of the three measurement points can be matched. Further, the research IDs of the questionnaires are definite relatable to the log-in names of the portal (user data) and the research IDs used for the routine data of the health insurance. The analysing institutions keep a record about the return of the patient questionnaire in an Excel-Sheet. The ID of returning questionnaires will be reconciled with the ID of cases in the SPSS data files.

Codebooks will be prepared for the questionnaires. Scanning is used for the data entry of the patient questionnaires. The team member entering the data can immediately correct data which was incorrectly inserted by the computer system. The data of 10% randomly selected questionnaires will be double-checked. If more than 5 ‰ of the data entries are incorrect, all data will be entered twice. The patient questionnaires will be checked for plausibility of age and gender. The checks include that the gender is reported identically across all three measurement points and that there is only 1 year of difference between the measurement points t0 and t2. For all items there will be a range check of data values. As the physician questionnaires are completed primarily online, there will be no double entry of data but there will be plausibility checks comparable to the patient questionnaires.

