#### Analysis of physicians‘questionnaire data

The data analysis is primarily exploratory. The primary outcomes will be analysed using inferential statistics methods. IG and CG will be compared across the three measurement points. Statistically adjusted comparisons of means between IG and CG as well as across the three measurement points (using propensity scores) will be conducted. The characteristics of the practices and the user data of the online platform will be used as control variables. Before the calculations, the missing data processes, singular missing data and the drop-out of patients will be analysed. Recommendations regarding the handling of missing data in order to correct information biases will be considered [33]. If data is missing completely at random or missing at random, missing data will be imputed using the expectations-maximation algorithm. Moreover, there will be sensitivity analyses to assess the influence of missing data processes.

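### Only control-group physicians are offered paper questionnaires, so any effect of survey mode or of who responds falls on one arm of a comparison listed as primary

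*Protocol article*

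**What the plan says.** All references are to the protocol article.

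- **Mode.** Procedures for physicians states: "Physicians in the IG are interviewed online, physicians in the CG via an online survey or, where appropriate, paper-pencil questionnaires (hybrid survey". The same paragraph applies this to the main instruments in both arms: "Physicians in IC and CG fill out the primary outcome questionnaires at the following time points", followed by t0, t1 and t2.
- **Status of the outcome.** Table 2 (Outcomes) has a block headed "Quality of the patient-physician communication (physician"), with four instruments given at t0, t1 and t2. The primary hypothesis (Methods) is that informedness and communication "are rated significantly higher by general practitioners and patients who use the portal".
- **Analysis.** The section on physicians' questionnaire data calls the analysis primarily exploratory, then adds "The primary outcomes will be analysed using inferential statistics methods" and "IG and CG will be compared across the three measurement points". On adjustment it says "The characteristics of the practices and the user data of the online platform will be used as control variables". Survey mode is not among these variables.
- **Extent of paper.** Data management says: "As the physician questionnaires are completed primarily online, there will be no double entry of data". The sentence goes on to provide plausibility checks like those for the patient forms.
- **Patients.** Procedures for patients gives both arms the same schedule: t0 and t1 in the practice, t2 by post.

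**The concern.** A randomised comparison of self-ratings needs the outcome to be collected in the same way in both arms. Here the option of paper depends on allocation. This matters in two ways:

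- **Measurement.** If physicians rate their own communication differently on paper than online, the difference occurs only in the control group.
- **Response.** A physician who would answer only on paper can be counted in the control group but is lost in the intervention group.

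Both would be read as part of the portal effect. The physicians are unblinded, the ratings are subjective, and the rule already applies at t0, so the baseline values share the imbalance. At stake is the physician-rated half of the primary hypothesis.

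**Working it through.** **1. The plan's own figure.** The only effect-size calculation for the primary outcomes is the patient one (Sample size calculation): effect 0.30 SD, power 0.80, alpha 2.5%, 2:1 allocation. Sidedness is not stated; two-sided is assumed.

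Control n = (1 + 1/2) × (2.241 + 0.842)² / 0.30² = 158.4, so 159 control and 318 intervention, against 160 and 320 stated. With the design effect, 320 × 1.09 = 348.8 and 160 × 1.09 = 174.4. After 35% dropout, 349/0.65 = 536.9 and 175/0.65 = 269.2. The figures reproduce and do not depend on survey mode. They describe patients, so 0.30 SD is only a rough yardstick for physician ratings.

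**2. How mode enters the contrast.** Let s be the share of control responders on paper and m the shift in ratings that paper causes, in SD. No intervention physician uses paper, so the intervention-minus-control difference moves by −s × m. For response, let q be the share of control responders who would answer only on paper, and d their mean difference from the others. If their counterparts in the intervention group do not reply, the contrast moves by −q × d. The document gives none of s, m, q or d, so neither size nor sign is known.

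**3. Illustration with assumed values.** There are 150 physicians (Participants and recruitment), about 100 versus 50 if practices are of similar size. Ignoring clustering, SE = √(1/100 + 1/50) = 0.173 SD. Actual type I error at nominal two-sided 2.5% is 1 − Φ(2.241 − b/SE) + Φ(−2.241 − b/SE), with b = s × |m|.

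| s (assumed) | m (assumed) | b | b / 0.30 | Type I error |
|---|---|---|---|---|
| 10% | 0.1 SD | 0.01 | 3% | 2.5% |
| 25% | 0.2 SD | 0.05 | 17% | 3.1% |
| 50% | 0.2 SD | 0.10 | 33% | 5.1% |
| 50% | 0.3 SD | 0.15 | 50% | 8.6% |

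The largest shift is 0.15/0.173 = 0.87 of a standard error. The table shows raw comparisons at one time point, with no use of t0.

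**4. What the t0 measurement removes.** In a change from baseline, the shift becomes (s at t1 − s at t0) × m. It is zero if every physician keeps the same mode. If the paper share went from 10% at t0 to 25% at t1, with m = 0.2 SD, it would be 0.15 × 0.2 = 0.03 SD. The article does not require a constant mode, and a change score does not deal with selective response.

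**5. What adjusting for mode could do.** The paper-by-intervention cell is empty. A mode effect could be estimated only within about 50 control physicians, among whom paper is not assigned at random. That is a weak basis for correction.

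**The case against.** The strongest reply is that the asymmetry is small and falls on a lesser part of the trial. Control physicians may also answer online, and Data management expects mainly online completion, so paper is the exception. The physician analysis is labelled primarily exploratory. Baseline values exist, and that analysis section plans to examine missing-data processes, with sensitivity analyses. Intervention physicians have enrolled to use an online portal, so an online form is probably little obstacle to them. The exact conditions for paper may be set out in a full protocol that is not shown.

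Most of this stands as a limit on size. It does not remove the point: offering paper to one arm only is a stated choice, the outcome is listed as primary and tested inferentially, and the planned missing-data work does not address mode.

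A reader might infer more than the document supports:

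- **That mode and treatment are fully confounded.** They are not, because both arms include online responders.
- **That the bias favours the intervention**, because physicians who prefer paper drop out of that arm and are the lighter portal users. Nothing in the article supports either step.
- **That waiving double entry biases the control arm.** The same sentence keeps plausibility checks, and errors on a few forms would mainly add noise.
- **That the two effects can never be separated afterwards.** A comparison restricted to online responders is possible if mode is recorded, although it does not remove selection.

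**Conclusion.** The point holds in a limited form. Paper is available only to control physicians for a primary-listed outcome at all three time points, so any mode effect and any mode-related difference in response partly enter the arm contrast. Direction and size cannot be derived from the document. Under the assumed ranges (10% to 50% of control physicians on paper, 0.1 to 0.3 SD mode effect, about 100 versus 50 physicians, no clustering, no baseline adjustment), the shift is 0.01 to 0.15 SD and the type I error 2.5% to 8.6%. Mainly online completion makes the lower part of these ranges more plausible. The t0 values remove a stable mode effect only for physicians who keep one mode, and adjustment for mode is weak. The patient-rated outcomes and the sample size are untouched. This is an inexpensive improvement to the physician comparison and no threat to the trial as a whole.

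**What to change.** Apply one mode rule to both arms at t0, t1 and t2: online first, with the same paper option on the same terms. Keep the portal items as a separate section for the intervention group only, so that the shared instruments are identical. Record the mode of every physician questionnaire, report response by arm and mode, and add a sensitivity analysis restricted to online responders, noting that it does not correct for who chose paper.

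The cost is printing and entering a small number of extra paper forms among about 150 physicians, plus one recorded variable and one additional analysis.

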
#### Procedures for patients

In both IG und CG all patients with back pain receive brief study information at their first consultation and are invited to participate in the study. If interest is expressed, the physicians will inform the patients and enrol them in the study. Each enrolled patient will receive a patient number consisting of a three-digit practice number, a two-digit physician number and a two-digit patient number (e.g. 543/09/01). This number matches the number of their questionnaire. Each physician receives questionnaire packages for 10 patients including: envelope with the t0 and t1 questionnaires and the log-in name for the portal (if patient is in IG). The packages are prepared by the Section of Health Care Research and Rehabilitation Research (SEVERA) on the basis of a pseudonymised list of all participating practices. After enrolling a patient, the medical practice immediately contacts the UHE and forwards the questionnaire number (patient number), contact information, written consent for study participation and permission for data usage to the UHE. Written consent must be received by the UHE in order to allow the UHE to send the t2 questionnaire along with a book voucher 3 weeks after consultation. Patients in IG and CG complete questionnaires on informedness, physician-patient communication, health literacy and self-efficacy at three measurement points: in the doctor’s office before (t0) and after (t1) consultation and 3 weeks later by post (t2). Patients in the CG receive consultation and care as usual not limited or influenced by this study. For patients in the IG the physician uses the explanatory material of the back pain portal, selects information and sends it as a printout or by email. The doctor encourages the patients to study the provided material, to access the online portal and to implement the given recommendations. With the log-in name received in the practice, patients in the IG can access the portal after their consultation. Usage frequency of the portal per patient is checked via web analytics and serves as indicator for intervention adherence. There are no other restrictions or requirements by the study protocol for additional care of the patients in the IG. Further consultations are covered by the health care system. Doctors and patients of the IG are free to continue using the portal during the study. Compensation for using the portal in consultation can only be charged once per patient. 50 randomly selected patients from the IG will be interviewed by SEVERA after completion of the postal survey (t2) in semi-structured 45- to 60-min telephone interviews on acceptance, quality and practicability of the portal as well as satisfaction with the counselling process and the perception of their own and the physician’s communication. Numbers and reasons of discontinuation of intervention and of lost to follow up will be given (Fig. 1).

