### Generation and concealment of allocation sequence and implementation of allocation

The participating practices are allocated in a 2:1 ratio of IG to CG. The allocation will be stratified by number of participating physicians within a practice (1 physician vs. 2–4 physicians vs. more than 4 physicians). The allocation sequence will be computer generated and concealed until time of allocation. The UHE will recruit the practices, while the MPS will generate the allocation sequence. The UHE will send a list with the research numbers of the practices and the stratification characteristics to the MPS which adds the information about group allocation according to the randomly generated sequence.

The UHE will inform the practices about their allocation. This procedure ensures that neither the recruiting nor the analysing institutes can influence that a particular practice will be allocated to either IG or CG.

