### Blinding/masking

Due to the nature of the intervention, participants (physicians, patients) will be aware of their allocation status and cannot be blinded. Also, the assessment of the evaluators cannot be blinded, since the number of cases will differ between IG and CG, questionnaires for the IG will contain additional variables, and it is possible that further questions regarding the routine data of the health insurance arise.

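### Unblinded physicians enrol patients after practice allocation; inviting all patients is not reconciled with 10 packages per physician, and no enrolment order or pre-enrolment count would show differential recruitment

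*Protocol article*

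**What the plan says.** All statements are in the protocol article.

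- **Allocation.** Practices are randomised 2:1. Under Generation and concealment of allocation sequence: "The UHE will inform the practices about their allocation". Under Blinding/masking: "participants (physicians, patients) will be aware of their allocation status and cannot be blinded".
- **Invitation.** Under Procedures for patients, in both arms, "all patients with back pain receive brief study information at their first consultation and are invited to participate in the study".
- **Enrolment.** In the same section: "If interest is expressed, the physicians will inform the patients and enrol them in the study".
- **Capacity.** Also there: "Each physician receives questionnaire packages for 10 patients". The intervention-group package holds the portal log-in name.
- **Pool.** Under Participants and recruitment, over five quarters, "the resulting recruitment potential is 50 to 60 patients per physician".
- **Payment.** Under Procedures for physicians, both arms receive 34 € per participating patient. Intervention-group physicians receive a further 40 € "once per patient for the first consultation using the portal".
- **Reporting.** Procedures for patients and the caption of Fig. 1 promise numbers and reasons for stopping the intervention and for loss to follow-up.
- **Outcomes.** In Table 2 the patient-rated communication scales (SDM-Q-9, KOVA, P.A.INT Satisfaction) are marked at t1 only.
- **Adjustment.** Under Analysis of patients' questionnaire data, a propensity score adjustment is considered if the arms turn out imbalanced.

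**The concern.** Randomising practices makes the practices comparable. It does not by itself make the patients comparable when they enter later through someone who knows the arm. The stated concealment procedure covers which arm a practice gets, not who is enrolled afterwards.

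Three features leave room for the two arms to recruit differently:

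- The number of packages is small against the stated potential, and the text does not say when invitation starts, whether it stops at ten, or in what order interested patients are taken.
- Enrolment is a different act in each arm. In the intervention group it leads to a consultation with the portal and to the additional fee. In the control group it leads to usual care.
- No count of patients before enrolment is described, so departures from the invite-all statement would leave no trace.

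What is at stake is the patient-rated primary comparison. If the enrolled patients differ between arms in traits that influence how a consultation is rated, that difference would be read as a portal effect. A larger sample does not remove such a bias. It makes a false-positive result more likely.

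**Working it through.** **1. The plan's own figures reproduce.**

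- Recruitment potential: 900 patients × 0.20 insured by a company fund × 0.30 with back pain = 54, inside the stated 50 to 60.
- Planned intake: 150 physicians × 10 packages = 1500, exactly the recruitment target. Ten is also the cluster size in the design effect, 1 + 0.01 × (10 − 1) = 1.09.
- Primary sample size, with effect 0.30, power 0.80, alpha 2.5% two-sided and 2:1 allocation: control n = 1.5 × (2.241 + 0.842)² / 0.30² ≈ 159, so 318 in the intervention group (stated 160 and 320). With the design effect, 320 × 1.09 = 348.8 and 160 × 1.09 = 174.4 (stated 349 and 175). With 35% dropout, 349 / 0.65 = 537 and 175 / 0.65 = 269.2, rounded up to 270 (as stated).

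None of these figures is in dispute. They confirm the two-sided 2.5% level used in step 4.

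**2. Packages against potential.** 10/60 = 17%, 10/54 = 18.5%, 10/50 = 20%. The potential is derived from prevalence. It does not count patients who present, qualify, are interested and consent, so these shares are not enrolment fractions among consenting patients. They show only that the documents themselves expect more candidates than packages.

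**3. Incentive by arm.** Control: 34 € per patient. Intervention: 34 + 40 = 74 € once the portal is used in the consultation.

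**4. What a difference in patient mix would do (illustration).** The documents give no figure for the bias, so b is an assumption, in SD units of the outcome. With no true effect:

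- Analysed numbers: 1000 × 0.65 = 650 and 500 × 0.65 = 325. The primary-outcome requirement of 349 and 175 is shown as well.
- SE = √[1.09 × (1/650 + 1/325)] = 0.0709. For 349 and 175, SE = √[1.09 × (1/349 + 1/175)] = 0.0967.
- False-positive rate = Φ(b/SE − 2.241) + Φ(−b/SE − 2.241).

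| Assumed b (SD) | 349 / 175 analysed | 650 / 325 analysed |
|---|---|---|
| 0 | 2.5% | 2.5% |
| 0.05 | 4.5% | 6% |
| 0.10 | 11% | 20% |
| 0.15 | 25% | 45% |
| 0.20 | 43% | 72% |

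A value of 0.10 SD is one third of the planned effect of 0.30.

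**5. What could correct it.** The t1-only communication scales rate a consultation, so they have no earlier value to adjust for. Adjustment must use other t0 variables. Tables 2 and 3 list self-reported knowledge, PEPPI, HLQ, pain VAS, Back Belief Questionnaire, internet use, sociodemographic and medical data. Self-reported knowledge does give the informedness outcome a baseline. No listed variable captures rapport with the physician or the time available on the day.

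**The case against.** The strongest reply is that the article does state a rule: all patients with back pain are invited at first consultation, in both arms, and enrolment follows from the patient's interest. Followed until the packages run out, this comes close to consecutive enrolment. That is a fair reading, and it is why the point is a missing reconciliation and not an absent rule. But the text does not say that this is how the packages are to be used, and it describes no record by which compliance could be checked.

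A reader might infer something stronger: that each physician picks the 10 most suitable of about 54 eligible patients. The documents do not support this. They never say that physicians choose, and 54 is a potential. They state no hard cap either, since the two-digit patient number allows more than ten. A bias of 0.10 SD can be derived that way (selection intensity 1.44 × assumed correlation 0.07 = 0.10). It requires intervention physicians to rank all 54 patients at once while control physicians enrol at random. Patients arrive over five quarters and must volunteer, so this should not be read as an estimate.

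Other replies stand in part:

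- The additional fee rewards use of the portal. It gives a reason to enrol more patients, and any motive to enrol particular kinds of patient is conjecture. Control practices also have work to do on enrolment: information, consent, questionnaires and forwarding of documents.
- The t0 variables include internet use, so some imbalance can be seen and partly adjusted, but the propensity adjustment is only considered.
- Enrolment order and logs might be in the practices' instruction manual, and the boxes of Fig. 1 cannot be judged because the figure is not shown. Against this, the Publication plan describes the present paper as the full trial protocol, so deferral to another protocol is a weak answer.

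**Conclusion.** The point holds in limited form. Patients are enrolled after allocation by physicians who know the arm, and the consequences of enrolment differ by arm. The invite-all statement is not reconciled with 10 packages per physician, and the counts promised in the text begin only after enrolment. Differential recruitment could thus bias the patient-rated primary comparisons unseen, with only partial means of adjustment.

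Neither the size nor the direction of any bias can be derived from the documents. The rise from 2.5% to about 20% rests on an assumed 0.10 SD difference in patient mix, no true effect, 650 and 325 analysed, and the plan's design effect of 1.09. At 0.05 SD the rate would be about 6%. The figures show that a modest difference would matter at this sample size, not that one will occur. No sample-size figure changes. The change is worth making because it is cheap and addresses a bias that randomising practices cannot prevent and analysis can only partly repair.

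**What to change.** In Procedures for patients, for both arms:

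1. State that each physician invites consecutive eligible patients with back pain from a fixed start date and enrols those who consent until the 10 packages are used. This reconciles the invite-all statement with the packages.
2. Have the practice keep a short anonymous tally of eligible, invited and consenting patients up to the tenth enrolment, and report these counts by arm in the flow diagram.
3. Compare the t0 characteristics of enrolled patients by arm.

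The cost is a change to the practice instructions, one line of paperwork per eligible patient, and less freedom for practices over when they recruit. Consecutive enrolment reduces the room for differential recruitment, and the tally exposes what remains. Neither removes the effect of patients' own decisions to take part when the arm is known.
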